## Abstract

**Background:**

Hyperglycemia in pregnancy is associated with poor perinatal outcome. Even if pregnant women with diabetes are monitored according to current guidelines, they do much worse than their normoglycaemic counterparts, marked by increased risks of pre-eclampsia, macrosomia, and caesarean section amongst others. Continuous Glucose Monitoring (CGM) is a new method providing detailed information on daily fluctuations, used to optimize glucose control. Whether this tool improves pregnancy outcome remains unclear. In the present protocol, we aim to assess the effect of CGM use in diabetic pregnancies on pregnancy outcome.

**Methods/design:**

The GlucoMOMS trial is a multicenter open label randomized clinical trial with a decision and cost-effectiveness study alongside. Pregnant women aged 18 and over with either diabetes mellitus type 1 or 2 on insulin therapy or with gestational diabetes requiring insulin therapy before 30 weeks of gestation will be asked to participate. Consenting women will be randomly allocated to either usual care or complementary CGM. All women will determine their glycaemic control by self-monitoring of blood glucose levels and HbA1c. In addition, women allocated to CGM will use it for 5–7 days every six weeks. Based on their CGM profiles they receive dietary advice and insulin therapy adjustments if necessary. The primary outcome measure is rate of macrosomia, defined as a birth weight above the 90th centile. Secondary outcome measures will be birth weight, composite neonatal morbidity, maternal outcome and costs. The analyses will be according to the intention to treat principle.

**Discussion:**

With this trial we aim at clarifying whether the CGM improves pregnancy outcome when used during diabetic pregnancies.

**Trial registration:**

Nederlands Trial Register: NTR2996

## Background

Diabetes during pregnancy is a high risk situation for both mother and the child. Optimising glycaemic control is a key feature of prenatal care for diabetic women [1]. Since the 1960s, there has been a reduction in perinatal morbidity and mortality [2,3]. However, even if pregnant women with diabetes are monitored according to current guidelines, they do much worse than their normoglycaemic counterparts. In a nationwide study in 2000 on the outcome of 323 women with a pregnancy complicated by type 1 diabetes we found a high prevalence of maternal, perinatal and neonatal complications [4]. These complications occurred despite good pre-pregnancy care, as 84% of these pregnancies were planned and 70% used adequate folic acid supplementation. Overall, glycaemic control during these pregnancies was acceptable, as average HbA1c value was 44 mmol/mol. Nevertheless, these pregnancies showed high complications rates that require improvement.

The continuous glucose monitoring system (CGMS) is a new technique that retrospectively provides detailed information regarding glucose fluctuations during the day. The CGMS has been studied in non-pregnant patients where it has demonstrated clinical usefulness by enhancing decision-making through detecting previously unrecognised postprandial hyperglycaemia and nocturnal hyper-and hypoglycemia [5]. Scientific evidence on a HbA1c-reducing effect of CGMS use is limited [6,7]. Although some studies do evaluate the effect of CGMS use on biochemical endpoints, such as HbA1c levels, data on clinical endpoints like diabetic complications, are lacking. The usefulness of CGMS use during pregnancy has hardly been evaluated up to now [7]. A recent RCT showed that intermittent CGMS use during pregnancy in 71 women with pre-existing diabetes resulted in a significant reduction in HbA1c at 32–36 weeks gestation. Furthermore, the odds ratio for reduced risk of macrosomia was 0.36 (95% CI 0.13-0.98, p = 0.05) [8]. However, this study was hampered by small sample size and both study groups differed in composition (e.g. 5 set of twins in the intervention group as opposed to none in the control group). Furthermore 11 (4%) of the children in the intervention group were small for gestational age (≤10 centile) as opposed to none in the control group. This difference did not reach statistical significance either but may point to an adverse effect of CGMS. Another recent RCT by Secher et al. investigated the effect of intermittent real time CGMS use during pregnancy in 154 women with pre-existing diabetes on pregnancy outcome [9]. The rate of macrosomia was not significantly different between the intervention group (43%) and the control group (30%) (p = 0.09). Also, HbA1c levels were similar in both groups. The investigators concluded that intermittent CGMS use did not improve glycaemic control in pregnancy nor did it improve pregnancy outcome. Thus, further evaluation in larger studies is urgently needed before wide implementation of CGMS during pregnancy.

### Relevance

Despite improvements in blood glucose monitoring technology, and obstetric and neonatal care over the last decades, maternal and fetal complications occur much more frequent in diabetic women than in non-diabetic women [4]. Our Dutch nationwide study of type 1 diabetes mellitus in pregnancy showed high complication rates in diabetes pregnancies. Maternal complications were episodes of severe hypoglycemia (40%), pre-eclampsia (13%) and caesarean section (44%). Perinatal and neonatal complications included congenital malformations (9%), prematurity (32%), perinatal mortality (3%), macrosomia (45%) and neonatal morbidity such as shoulder dystocia (14%), all remarkably higher rates than those in non-diabetic pregnancies [4]. Similar rates of complications have recently been found in other nationwide studies in Denmark, the United Kingdom and Sweden [10-12]. In the Dutch study 45% of the newborns were macrosomic and 24% were extremely macrosomic (>p97.7). Recent data from Denmark show that 56% of the newborns of type 2 diabetic women were macrosomic [11].

The prevalence of gestational diabetes is increasing and comprises approximately 5% of the pregnant women. Given the worldwide rising incidence of diabetes, as a consequence of changed life style and consequent obesity, improvement of obstetric care for diabetic patients is essential [13,14]. Moreover, it has been shown that children born macrosomic are at risk for developing obesity and diabetes mellitus type 2 at a young age [15-17]. Reduction of macrosomia will not only reduce the risk of perinatal complications but may also prevent these future health problems.

## Methods/design

### Aims

This trial evaluates the clinical effectiveness, costs and cost-effectiveness of CGMS use with the aim to optimize glycaemic control and pregnancy outcome of diabetic pregnancies relative to standard control methods. The primary outcome measure is macrosomia. Secondary obstetric outcome measures are birth weight, neonatal and maternal morbidity. Furthermore, diabetic outcome measures are HbA1c level, and glucose variability. In addition, cost-effectiveness will also be evaluated.

### Study design

The study will be a multicentre randomised controlled trial comparing standard care to standard care with additional CGMS use. The study will be open, as it is impossible to blind the pregnant women and health care workers involved for the strategy to which the women are allocated. This trial is performed by the Dutch Obstetric Consortium, a collaboration of the majority of hospitals in the Netherlands. It supplies research nurses and online services, and is supported by the Dutch Society of Obstetrics and Gynaecology. Approximately 25 hospitals, including university hospitals, teaching hospitals and non-teaching hospitals will participate in this trial.

The study has been approved by the ethics committee of the Academic Medical Centre Amsterdam (reference number 10/322 # 11.17.0554) and in addition by the boards of management of all participating hospitals.

### Participants

Pregnant women with pre-existing diabetes mellitus (type 1 or 2) before gestational age of 16 weeks or with gestational diabetes requiring insulin therapy before 30 weeks gestational age will be asked to participate. Inclusion criteria include maternal age of at least 18 years and need for insulin treatment by means of injections or insulin pump. Patients with severe medical or psychological comorbidity will be excluded. Multiple pregnancies will also be excluded since they require different standards of obstetric evaluation.

### Recruitment and randomisation

Potential study candidates will be identified by their gynaecologist or internist. Patients eligible for participation in the study will be invited for additional counselling by a research nurse, to ensure that they will be fully informed on the nature of the study by means of both oral and written information. Patients who agree to participate will be asked to sign a written informed consent of which they will receive a copy.

After providing informed consent for the participation in the study, the patient will be randomly allocated to either standard care or standard care and additional CGMS use. Randomisation will be done on a 1:1 basis over the internet, stratified for type of diabetes, using a web-based program. The current inclusion status is being displayed on the GlucoMOMS trial website http://www.studies-obsgyn.nl/glucomoms/page.asp?page_id=1027

### Hypothesis

The CGMS has been shown to potentially improve glycaemic control as defined by HbA1c levels. Since obstetric complications in diabetic pregnancies, especially macrosomia, seem to be related to glycaemic control, we hypothesise that the additional use of CGMS will reduce the macrosomia rate by 30 percent.

### Intervention

The continuous glucose monitoring system (CGMS) is a new technique that is efficacious in the monitoring of diabetic women. It can provide a comprehensive glucose profile over a 5–7 days period. The CGMS (CGMS Medtronic: Minimed, Northridge,CA) measures glucose levels through electro-chemical detection in the extracellular fluid of the abdominal subcutaneous tissue and stores values in a range of 2.2 - 22.2 mmol/L every 10 sec. An average value is stored in the monitor every 5 minutes, providing up to 288 blood glucose measurements (12x24) a day. The subjects are unaware of the results of the sensor measurements during monitoring and need to continue self-monitoring of blood glucose while carrying the monitor. After 5–7 days glucose profiles are obtained from the monitor and can be evaluated by the diabetologist and dietary or insulin therapy changes can be advised.

All study participants will determine their glycaemic control by self-monitoring of blood glucose levels (4–8 times/day) and HbA1c-levels (every 4 weeks) throughout the course of pregnancy. Figure 1 represents a flowchart of the study.

**Figure 1 F1:**
[figure not shown]
Flowchart.

### Outcome measures

#### Main study parameter/endpoint

Outcome measures of the trial are related to obstetric complications and glycaemic control. Macrosomia is the most frequent complication of diabetes during pregnancy and is associated with neonatal morbidity and long term effects. Therefore, the primary outcome measure is macrosomia rate. Macrosomia is defined as a birth weight above the 90^th^ centile.

Secondary maternal endpoints are: pre-eclampsia (defined as systolic blood pressure ≥ 140 mmHg or diastolic blood pressure ≥ 90 mmHg occurring after 20 weeks of gestation and simultaneous proteinuria of ≥300 mg/24 hours) caesarean section, hypoglycemia (subdivided as biochemical hypoglycemia (self-measured blood glucose < 3.9 mmol/l) or symptomatic hypoglycemia (symptoms of hypoglycemia confirmed by self-measured blood glucose < 3.9 mmol/l) or severe hypoglycemia, (prompting the need for help by another person)), HbA1c levels throughout the course of pregnancy, glucose variability (Mean Absolute Glucose change per patient per hour) and relative glucose variability (Coefficient of Variability) [18].

Secondary neonatal endpoints are: birth weight, preterm birth, perinatal death, birth trauma (including shoulderdystocia, clavicle fracture or Erb’s palsy), neonatal hypoglycemia (defined as blood glucose < 2.6 mmol/l), respiratory distress syndrome (RDS), broncho pulmonal dysplasia (BPD), intraventricular haemorrhage II B or worse, necrotizing enterocolitis (NEC), and sepsis.

#### Follow up

Long term follow up of the offspring is desirable as long term effects of diabetic pregnancy on infants, in particular those born macrosomic, have become evident. Long term follow up is planned but will depend on future funding.

#### Economic evaluation / cost analysis

With two or three continuous glucose monitors (hardware), costing about €1,500 each, the total monitor costs are €37,500 per centre. We will use 5 sensors (each €50) per pregnancy, resulting in sensor costs of €37,500, bringing total equipment costs at €75,000. The additional costs of CGMS per year (per pregnancy) are €500. With these crude estimates, a hypothesized 33% reduction in macrosomia rate, would imply for the short term a cost-effectiveness ratio of €1,500 per prevented case of macrosomia, €6,076 per prevented caesarean section, €15,189 per prevented case of preterm birth, and €48,605 per prevented case of neonatal death. A strong reduction of macrosomia would also reduce downstream resource use and associated costs of neonatal complications. The question is to what extent downstream economic benefits also offset the costs required to obtain these clinical outcomes, and whether the resulting cost-to-benefit ratio justifies a standard policy of using CGMS during pregnancy [19,20].

Rising health care costs and reimbursement of expensive medical devices are not justified unless extensive cost-effective analysis turns out favourable. Therefore, besides evaluation of the effectiveness of CGMS on pregnancy outcome, resource utilization and costs for maternal and neonatal care will be analysed as well.

### Statistics

#### Sample size

We anticipate that a reduction of macrosomia from 45% to 30% will outweigh the costs of the additional use of the CGMS. As we assume 10% protocol violations and drop out, we need to randomise 300 women (Alpha-error .05, Beta-error .20, one-sided test) of which 150 will receive additional CGMS use and 150 will be controls.

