#### Data analysis

Data will initially be analysed according to the intention to treat method. The main outcome variable, macrosomia, will be assessed by calculating rates in the two groups, relative risks and 95% confidence intervals as well as numbers needed to treat. The secondary outcome measures will be addressed in a similar manner. Continuous outcome measures will be compared using parametric and non-parametric tests, depending on the distribution of the data. We plan a subgroup analysis of women with diabetes type 1 and type 2 diabetes and gestational diabetes.

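### The sample size is set for a one-sided 5% test, but the primary outcome is assessed with a 95% confidence interval, against which 300 women give about 72% power

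*Protocol article*

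**What the plan says.** - **Design effect (Sample size).** "We anticipate that a reduction of macrosomia from 45% to 30% will outweigh the costs of the additional use of the CGMS".
- **Test and size (Sample size).** "we need to randomise 300 women (Alpha-error .05, Beta-error .20, one-sided test", split equally between the arms: "of which 150 will receive additional CGMS use and 150 will be controls".
- **Allowance (Sample size).** "As we assume 10% protocol violations and drop out". This is one combined figure; violations and drop-out are not separated.
- **Primary analysis (Data analysis).** Macrosomia is assessed by the rates in the two groups, "relative risks and 95% confidence intervals as well as numbers needed to treat". No one-sided test, one-sided bound or 90% interval is named there.
- **Analysis set (Data analysis).** "Data will initially be analysed according to the intention to treat method".
- **Earlier evidence (Background).** Two randomised trials in pregnancy are cited. One, in 71 women, favoured CGM for macrosomia (odds ratio 0.36, 95% CI 0.13 to 0.98). In the other, in 154 women using real-time CGM, "The rate of macrosomia was not significantly different between the intervention group (43%) and the control group (30%) (p = 0.09").

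The protocol gives no reason for choosing a one-sided test.

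**The concern.** The power statement and the reported inference use different error rates. A one-sided 5% test corresponds to a one-sided 95% bound, that is, to one limit of a 90% interval. A conventional 95% interval is stricter on the benefit side: it excludes 1 only at one-sided 2.5%. The 80% therefore describes a criterion other than the one the analysis section sets out to report.

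Two things are at stake. First, a reader who judges the trial by its 95% interval will take the power to be 80% when it is lower. Second, a result can meet one criterion and fail the other. If the protocol does not say which governs, sidedness can be settled after the data are seen.

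A smaller, related issue is the 10% allowance. Inflating the sample replaces women who leave the analysis. Under intention to treat, protocol violators stay in it and may dilute the effect, which inflation for loss does not address.

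**Working it through.** **Inputs.** p1 = 0.45, p2 = 0.30, alpha 0.05, power 0.80, 150 per arm, 10% allowance (all from Sample size). Allocation is 1:1 (Recruitment and randomisation). If the whole 10% is lost, 150 × 0.9 = 135 per arm remain.

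**Formulas (pooled normal approximation).** With p̄ = (0.45 + 0.30)/2 = 0.375:

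- A = √(2 × 0.375 × 0.625) = 0.6847
- B = √(0.45 × 0.55 + 0.30 × 0.70) = 0.6764
- n per arm = (z_α·A + z_β·B)² / 0.15²
- power = Φ[(0.15·√n − z_α·A) / B]

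**Step 1: reproduce the plan's figure (one-sided 5%, z = 1.645).**

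- n = (1.1262 + 0.5693)² / 0.0225 = 127.8, so 128 per arm. Then 128/0.9 rounds up to 143 per arm, 286 randomised. With continuity correction: 141 per arm, 314 randomised. The stated 300 lies between the two.
- Power at 135 per arm: Φ[(1.7428 − 1.1262)/0.6764] = Φ(0.912) = 81.9%. With continuity correction it is 78.4%. The stated 80% is confirmed for the one-sided test.

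**Step 2: the same design against the 95% interval (z = 1.960).**

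- n = (1.3419 + 0.5693)² / 0.0225 = 162.3, so 163 per arm. Then 163/0.9 rounds up to 182 per arm, 364 randomised. Other two-sided formulas give about 355 to 392, so 300 follows only from the one-sided choice.
- Power at 135 per arm: Φ[(1.7428 − 1.3419)/0.6764] = Φ(0.593) = 72.3%.
- Power at 150 per arm, nobody lost and no dilution: Φ[(1.8371 − 1.3419)/0.6764] = Φ(0.732) = 76.8%.
- Checks at 135 per arm: exact power of the two-sided chi-square test 72.8%; Wald interval for the log relative risk, normal approximation, 70.5%.
- Effect detectable with 80% power, two-sided, 135 per arm: 45% v about 28.6%.

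**Step 3: how often the two criteria disagree.** The difference in power at 135 per arm is 81.9 − 72.3 = 9.6 points. Exact enumeration of all outcomes under 45% v 30% gives 9.3% for a significant one-sided chi-square test together with a 95% interval for the relative risk that includes 1. An example is 61/135 v 47/135: one-sided p = 0.041, relative risk (47/135)/(61/135) = 0.77, 95% CI 0.57 to 1.04.

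**Step 4: violators kept under intention to treat.** The protocol gives neither the split of the 10% nor the risk in violators, so these are assumed scenarios:

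| Assumption | Rates compared | n per arm | Power one-sided 5% | Power two-sided 5% |
|---|---|---|---|---|
| All kept, no dilution | 45% v 30% | 150 | 85.3% | 76.8% |
| 5% drop out, 5% of CGM arm at control risk (0.95 × 30% + 0.05 × 45%) | 45% v 30.75% | 142.5 | 80.1% | 70.0% |
| All kept, 10% of CGM arm at control risk (0.9 × 30% + 0.1 × 45%) | 45% v 31.5% | 150 | 77.9% | 67.4% |
| All kept, 10% crossover in both arms | 43.5% v 31.5% | 150 | 69.3% | 57.5% |

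These rows are alternatives to the 72.3% in Step 2. They do not add to it.

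**The case against.** **The 80% is not false.** The Sample size section openly names the test it belongs to, and for that test the figure is right. This stands: the arithmetic is sound, and the fault is the mismatch between two sections.

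**The decision rule is inferred.** The Data analysis section never says that success means an interval excluding 1, and the protocol does not use the word two-sided. The interval could be pure estimation beside a one-sided test, with the rule set in an analysis plan that is not shown. This stands in part. But the protocol itself fixes a one-sided alpha in one section and a 95% interval for the same outcome in another, and nothing in it connects them.

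**Stronger readings that the document does not support.**

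- *The intention-to-treat power is 67%.* A reader might infer this from the combined allowance. It requires that all of the 10% are violators, that none is lost, and that those in the CGM arm carry the full 45% risk. None of this is stated, and other assumptions give 57.5% to 76.8%. The intention-to-treat analysis is also described as the initial one, so the allowance may have been meant for a later analysis without violators.
- *The one-sided test hides harm that earlier evidence predicts.* The 43% v 30% result was not significant and came from real-time CGM, whereas here women do not see the readings during monitoring. The other cited trial favoured CGM, and the protocol states a directional hypothesis. The planned 95% interval would show an adverse effect. What remains is that mixed evidence calls for a stated reason for one-sidedness, and none is given.
- *Conflicting conclusions are likely.* They would arise in roughly 1 trial in 10 under the design effect: enough to need a rule, but not the usual outcome.

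**Conclusion.** The concern holds as a mismatch between sizing and analysis. With 300 women and 45% v 30%, power is about 82% for the declared one-sided 5% test when 10% have no outcome. Against a conventional 95% interval it is about 72% on the same loss, and about 77% if everyone is kept without dilution. No two-sided scenario examined reaches 80%.

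This rests on reading the 95% interval as two-sided, which is convention rather than the protocol's wording, and on the protocol's own rates. The 72% further assumes that the whole 10% is lost. Dilution by retained violators could lower power further, but the document does not allow a single figure for it.

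**What to change.** 1. **Preferred.** Declare a two-sided 5% primary test, matching the 95% interval of the relative risk. Restate the power: with 300 women and 10% without an outcome, about 72% for 45% v 30%; 80% power corresponds to 45% v about 28.6%.
2. **Alternative.** Keep the one-sided test, justify it against both trials cited in the Background, and name the one-sided 95% bound (one limit of a 90% interval) as the decision criterion.
3. **In either case.** Limit the 10% loss allowance to women without a birth weight, because violators stay in the intention-to-treat analysis. Give any dilution figure only as a labelled scenario with its range, for example, for a two-sided test, 70% with a 5%/5% split and 67% if 10% of the CGM arm carry the control risk and all are kept.

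The cost is wording only and no extra patients. Under the preferred option the stated power becomes less favourable. Restoring 80% power two-sided for 45% v 30% would take about 364 randomised women, but the correction does not depend on that.

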#### Data analysis

Data will initially be analysed according to the intention to treat method. The main outcome variable, macrosomia, will be assessed by calculating rates in the two groups, relative risks and 95% confidence intervals as well as numbers needed to treat. The secondary outcome measures will be addressed in a similar manner. Continuous outcome measures will be compared using parametric and non-parametric tests, depending on the distribution of the data. We plan a subgroup analysis of women with diabetes type 1 and type 2 diabetes and gestational diabetes.

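### Randomisation is stratified by type of diabetes, but the stated primary relative risk has no stratum term: a modest precision gain is available at no cost

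*Protocol article*

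**What the plan says.** Protocol article, Recruitment and randomisation: "Randomisation will be done on a 1:1 basis over the internet, stratified for type of diabetes, using a web-based program". Block size and the number of strata are not given. I take three strata: type 1, type 2 and gestational diabetes.

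Protocol article, Data analysis: "The main outcome variable, macrosomia, will be assessed by calculating rates in the two groups, relative risks and 95% confidence intervals", together with numbers needed to treat. Secondary outcomes are to be handled in the same way. The only role given to diabetes type is the sentence "We plan a subgroup analysis of women with diabetes type 1 and type 2 diabetes and gestational diabetes".

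On risk by type, the Relevance section gives 45% macrosomia from a Dutch type 1 cohort, and for type 2: "Recent data from Denmark show that 56% of the newborns of type 2 diabetic women were macrosomic". It gives no macrosomia rate for gestational diabetes, and the expected mix of types is not stated anywhere.

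**The concern.** If allocation is balanced within a factor that predicts the outcome, the variation in risk between strata cannot contribute to the difference between the arms. A two-group variance formula still counts it as noise. The reported standard error is then larger than the true sampling error of the estimate, so the interval is wider and the test more conservative than the design requires.

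The article stratifies on a factor that it has reason to think prognostic, and then describes a main comparison that does not use it. At stake is a little of the precision that stratified allocation makes available. Validity is not at stake.

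**Working it through.** **1. The plan's own figure.** Inputs from Sample size: 45% v 30%, one-sided 0.05, power 0.80, 10% loss, 150 per arm.

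- Per arm: [1.645·√(2·0.375·0.625) + 0.842·√(0.45·0.55 + 0.30·0.70)]² / 0.15² = (1.126 + 0.569)² / 0.0225, which rounds up to 128.
- After 10% loss: 128/0.9, which rounds up to 143 per arm, 286 in total (314 with a continuity correction). The plan states 300.
- With 150 × 0.9 = 135 evaluable per arm: (0.15·√135 − 1.126)/0.676 = 0.91, so power is 81.9%.

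So 300 is consistent with a rounded-up, unstratified, one-sided two-proportion calculation. I use 135 per arm below.

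**2. The point estimate does not change.** With equal arm sizes in each stratum, the Mantel-Haenszel weights give every event a factor of 1/2. The stratified relative risk is then (sum of CGM events)/(sum of control events), which is the crude relative risk. In simulation the two differed by 0 in every trial.

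**3. The reported standard error does change.** Let p be the mean control risk, q = (2/3)p the mean CGM risk (common relative risk 2/3), V the between-stratum variance of control risk, and n = 135.

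- Crude: n·Var(log RR) = (1−p)/p + (1−q)/q.
- Counted in error when strata are balanced: 2V/p².
- Ratio of standard errors = √[crude / (crude − 2V/p²)].

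Example, 45/56/34% in equal thirds: p = 0.45, q = 0.30, V = (0 + 0.11² + 0.11²)/3 = 0.00807. Crude = 1.222 + 2.333 = 3.556; excess = 2 × 0.00807/0.2025 = 0.080; ratio = √(3.556/3.476) = 1.011.

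Documented rates only, 45/56% in equal halves: p = 0.505, V = 0.055² = 0.003025. Crude = 2.95; excess = 0.0237; ratio = 1.004.

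Assumed 15% for gestational diabetes, equal thirds: p = 0.387, V = 0.0300. Crude = 4.466; excess = 0.402; ratio = 1.048.

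**4. Simulation of the test.** 40,000 trials per scenario, 135 per arm, balanced strata, one-sided 0.05, relative risk 2/3: crude test v Cochran-Mantel-Haenszel test. Gestational rates and stratum shares are assumptions.

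| Control risk, type 1/type 2/gestational | Shares | Crude SE too large by | Power, crude v stratified | Crude type I error |
|---|---|---|---|---|
| 45/56/34% | equal thirds | 1.1% | 82.5% v 83.3% | 4.8% |
| 45/56/30% | 40/30/30 | 1.5% | 80.9% v 81.7% | 4.5% |
| 45/56/25% | equal thirds | 2.4% | 79.2% v 80.4% | 4.2% |
| 45/56/20% | 40/20/40 | 3.4% | 72.2% v 74.0% | 4.0% |

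The type I error column is from the same scenarios with relative risk 1. The simulated excess in SE agrees with the formula.

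**5. What this does to an interval.** In the 25% row the mean SEs are 0.1727 and 0.1686. Around an observed relative risk of 0.667, exp(−0.405 ± 1.96·SE) gives 0.475 to 0.935 crude and 0.479 to 0.928 stratified.

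**The case against.** The strongest objection is that the article never calls the relative risk crude or unadjusted and does not exclude a stratified estimate. The full protocol and the SAP are not shown, and an article may leave such detail to them. That stands as a limit: the text is not wrong, and the stratified method may already be planned. But the section does describe the primary method, and it gives diabetes type a different role. The point is therefore a recommendation to use the randomisation strata and is not a charge of error.

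It is also fair to say that the size depends on inputs the article does not give. The 45% and 56% come from different studies in different countries, so they do not isolate an effect of diabetes type.

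A reader might infer three stronger things that the document does not support:

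- **That the estimate is biased or itself less precise.** With balanced strata it is the same number; only its reported uncertainty is inflated, and in the safe direction.
- **That the loss is as large as 63% v 67% power.** That figure needs an assumed 15% gestational rate and a two-sided test, whereas the sample size rests on a one-sided test. On the one-sided test the gain is about 1–2 points.
- **That the subgroup plan commits the trial to reading separate significance tests as evidence of different effects.** The article announces a subgroup analysis and no more. Whether an interaction test accompanies it can be left to the SAP. Subgroups would be small, about 135/3 = 45 evaluable per arm if the types are equally represented, which is a reason for care but not a fault in the text.

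**Conclusion.** The point holds as a free improvement of modest size. Computed as written, the primary analysis would report a standard error of the log relative risk about 1–3% too large and give up about 1–2 points of one-sided power, at an assumed gestational-diabetes macrosomia rate of 20–34%. The excess in standard error rises to about 5% at an assumed 15% and falls to about 0.4% on the documented 45% and 56% alone. The error is conservative and leaves the estimate unchanged.

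These figures assume three strata, balance within strata among the 135 evaluable women per arm, a common relative risk of 2/3 and the stratum shares shown. The gain grows with the spread of risk between types.

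**What to change.** State in Data analysis that the primary relative risk is a Mantel-Haenszel estimate stratified by type of diabetes, with a Mantel-Haenszel risk difference from which the number needed to treat is derived. A modified-Poisson model (robust variance) with treatment and type of diabetes would serve equally well. Apply the same approach to the binary secondary outcomes. If the full protocol or SAP already says this, the sponsor need only confirm it.

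Optionally, add that the planned subgroup estimates will be reported with a single treatment-by-type interaction test.

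The cost is one or two sentences. Diabetes type is already recorded at randomisation, so neither new data nor a change in sample size is needed.
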